## Abstract

**Background:**

At present, there is short of effective treatment for acute exacerbation of idiopathic pulmonary fibrosis (AE-IPF). The treatment of IPF with traditional Chinese medicine (TCM) has some advantages. However, the evidence is unclear whether TCM can be recommended as an effective therapy to treat AE-IPF. The purpose of the study is to explore the efficacy and safety of TCM for patients with AE-IPF.

**Methods:**

A randomized, double-blind, placebo-controlled, exploratory clinical trial will be performed. A total of 80 patients diagnosed with AE-IPF will be randomized into the intervention or control group. In addition to conventional treatment, the intervention group will be treated with Kangxianhuanji granule, and the control group will be given a placebo granule. The administration frequency is 10 g each time and two times daily. After 4 weeks of treatment, the patients were followed up for 12 weeks. The primary outcomes are treatment failure rate and all-cause mortality. Secondary outcome measures will include the length of hospitalization, overall survival, acute exacerbation rate, intubation rate, Modified British Medical Research Council (mMRC) score, the St George’s Respiratory Questionnaire idiopathic pulmonary fibrosis (SGRQ-I) score, and arterial blood gas analysis.

**Discussion:**

TCM may be beneficial in IPF. However, it has never been evaluated in patients with AE-IPF, who are incredibly prone to respiratory failure and have a high mortality rate. It is the first clinical trial to explore the efficacy and safety of TCM in the treatment of AE-IPF. This result will provide a basis for further study, which provides a high-quality evidence for the treatment of AE-IPF with TCM.

**Trial registration:**

Chinese Clinical Trial Registry ChiCTR1900026289. Registered on 29 September 2019.

## Background

Idiopathic pulmonary fibrosis (IPF) is a chronic, progressive, fibrotic lung disease of unknown etiology occurring in adults [1]. It is characterized by worsening lung function and leading to respiratory failure and death [2]. Post-diagnosis median survival of patients with IPF has been reported to range from 2 to 3 years [1, 3–6]. However, some IPF patients have experienced a rapid progression of respiratory failure, which is called acute exacerbation of IPF (AE-IPF). AE-IPF is one of the leading causes of deterioration and mortality of patients with IPF [7–9]. AE-IPF can occur at any stage of IPF, with a dangerous condition, rapid progress, high mortality, and poor prognosis. The incidence of AE-IPF reported in the literature was significantly different due to the lack of a unified diagnostic standard, research methods, and different populations. The annual incidence of IPF has recently been estimated at 5~10% in the official Clinical Practice Guideline [1]. In many prospective studies, the annual incidence rate was slightly higher than 20% [10–12]. According to reports, the median survival period is about 3–4 months, and the mortality rate during hospitalization after acute exacerbation is 55–80% [1, 11, 13]. Nearly 90% of patients with AE-IPF need to be treated in ICU [14], and those who survive after the first acute exacerbation have a mortality rate of more than 90% after 6 months [15]. Therefore, the prevention, early diagnosis, and active treatment of AE-IPF are the primary and arduous medical tasks in clinical practice. It is particularly important to carry out therapeutic research on AE-IPF.

Due to the critical condition, rapid progress, and poor prognosis of patients with AE-IPF, the research and understanding of AE-IPF have been deepened in recent years. However, the etiology and mechanism of occurrence are still unclear. AE-IPF is challenging to treat and has a poor prognosis. There are no clear and valid treatment measures and drugs. At present, hormones, anti-fibrosis, and anti-infection are mainly used, and the efficacy of these drugs is not accurate. There were some specific effects and advantages of IPF patients treated by traditional Chinese medicine (TCM) [16–18], but mostly focusing on the stable period. The treatment of AE-IPF with TCM is still in the exploratory stage. Based on the evidence of the potential advantages of TCM for IPF patients, we will perform the clinical pilot study investigating the efficacy and safety of TCM in the treatment of AE-IPF.

## Methods/design

### Objectives

This trial aims to explore the safety, efficacy, and feasibility of TCM (Kangxianhuanji granule) in patients with AE-IPF.

### Study design

This study is a randomized, double-blind, placebo-controlled exploratory clinical trial. After receiving written informed consent, the subjects who passed the screening criteria will be recruited and randomly divided into the intervention group or the control group at a ratio of 1:1. After 4 weeks of treatment, the patients were followed up for 12 weeks. The study flow chart is summarized in Fig. 1, and the timing of treatment and follow-up are detailed in Table 1.

**Fig. 1 Fig1:**
[figure not shown]
Flow chart for the intervention trial

**Table 1 Tab1:** Timing of treatment visits and data collection

	Baseline	Treatment			Follow-up		
	Day 0	Day 7	Week 2	Week 4	Week 8	Week 12	Week 16
	V1	V2	V3	V4	V5	V6	V7
**Sign informed consent**	**×**						
**Randomization**	**×**						
**Medical history**	**×**						
**Intervention**	**×**	**×**	**×**				
**Primary outcome**							
Treatment failure rate		**×**	**×**	**×**			
All-cause mortality		**×**	**×**	**×**	**×**	**×**	**×**
**Secondary outcomes**							
Length of hospitalization		**×**	**×**	**×**			
Overall survival		**×**	**×**	**×**	**×**	**×**	**×**
Acute exacerbation rate					**×**	**×**	**×**
Intubation rate		**×**	**×**	**×**	**×**	**×**	**×**
mMRC	**×**	**×**	**×**	**×**			**×**
SGRQ-I	**×**	**×**	**×**	**×**			**×**
Arterial blood gas analysis	**×**	**×**	**×**	**×**			

Abbreviations: *mMRC* Modified British Medical Research Council, *SGRQ-I* The St George’s Respiratory Questionnaire for Idiopathic Pulmonary Fibrosis

The protocol of the trial (version 2019.06.18.1.0.4.0, 18 June 2019) was approved by the ethics committees of the First Affiliated Hospital of Henan University of Chinese Medicine (No. 2019HL-063-01) and registered at www.chictr.org.cn on September 29, 2019 (ChiCTR1900026289). The sponsor of the study is the Henan University of Chinese Medicine. The funder has no role in study design, data analysis, or the decision to submit the report for publication. In order to ensure the scientific nature of the trial, the reliability of the data, and the safety of the participants, the sponsor has established a Data and Safety Monitoring Boards (DSMB) which consists of medical, clinical pharmacology, epidemiology, statistics, and ethics experts. The protocol follows the recommendations of the SPIRIT initiative [19].

### Sample size

It is the first exploratory study to explore the efficacy of TCM in patients with AE-IPF. At present, we have not found the research data of AE-IPF treated by TCM, and the formal sample size calculation is not possible. We referred to the calculation method of the minimum sample size in exploratory clinical research, 40 participants in the intervention group, and 40 in the control group (*N* = 80 in total). The result of this study will provide data for a formal sample size calculation for further study.

### Participants

AE-IPF is defined as a clinically significant acute respiratory disease with worsening respiratory symptoms. It is characterized by a new and widespread alveolar abnormality on lung computed tomography [7]. The diagnosis of AE-IPF will be based on the Standards of An International Working Group Report [7]. To promote recruitment as well as compliance, a green channel for participants to see the doctor was established, regular phone calls or WeChat reminders of the follow-up date, provision of education manuals, and reduce or exempt medical expenses. For those who are lost to follow-up, try to get in touch through as many channels as possible. If the data is missing due to dropouts, we will deal with it through statistical methods, such as the intention-to-treat (ITT) analysis.

### Recruitment

The recruitment process of participants mainly includes recruiting participants, screening qualified participants, and obtaining informed consent of participants. The following is our process of recruiting participants. First, we determined that the doctors in each research center are responsible for recruiting staff. Second, we formulated recruitment plans and needs. Third, we carried out recruitment publicity through recruitment advertisements, which were placed at the entrance of the ward. Fourth, all participants would be recruited in the ward. Fifth, each research center was responsible for receiving visiting participants by special personnel, and at the same time, we should also answer the questions from online consultants. Sixth, we should screen the eligibility of participants according to the inclusion and exclusion criteria and doctors’ clinical experience. Finally, we should give a detailed description of the clinical trial scheme for the qualified participants, and inform them of the possible benefits and risks.

#### Inclusion criteria

A confirmed diagnosis of AE-IPF;Age between 40 and 80 years;Without participation in other interventional trials in 1 month; andWith the informed consent signed.

#### Exclusion criteria

Pregnant or lactating women;Dementia, mental disorders, and reluctant partners;Complicated with heart failure (NYHA Class IV), or unstable hemodynamics, or hypertension (Grade-4), or severe cardiac arrhythmias (e.g., ventricular tachycardia, paroxysmal supraventricular tachycardia, ventricular flutter, and ventricular fibrillation);Complicated with other respiratory diseases (e.g., pulmonary thromboembolic, active tuberculosis, bronchiectasis, and pneumothorax);Have been treated for more than 7 days before inclusion in the study;Respiratory failure requiring invasive mechanical ventilation;Complicated with severe liver and kidney disease (cirrhosis, portal hypertension, dialysis, or after renal transplantation);Bedridden for various reasons; andAllergic to the study of drugs.

#### Withdrawal, dropout, and discontinuation

During the study period, the disease deteriorated (such as complicated with acute respiratory failure, acute myocardial infarction, or acute heart failure, etc.);Serious adverse events occurring in the study;Serious violation of the research protocol makes it difficult to evaluate the effect of the drug, such as not taking medicine on time or not participating in the follow-up on time;Unwilling to continue participating in clinical trials;Lost participants during the study.

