### Outcomes

#### Primary outcome

Treatment failure rate: The treatment failure is defined as the symptoms or signs that have not improved or worsened (intubation, treatment with a ventilator, etc.), or the occurrence of new significant symptoms and signs, or new infection, or death. The number of treatment failures in two groups was recorded during the treatment period (4 weeks).All-cause mortality at 16 weeks (end of the follow-up): The number of deaths will be recorded at 16 weeks.

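### Deterioration and serious adverse events are grounds for leaving the trial, stopping the granule is not separated from leaving follow-up, and ITT is named as the remedy, so deaths by week 16 may be missed

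*Protocol article*

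**What the plan says.** In the protocol article, one section headed "Withdrawal, dropout, and discontinuation" lists the reasons for all three. The first is deterioration: "During the study period, the disease deteriorated (such as complicated with acute respiratory failure", followed by cardiac examples. The second is "Serious adverse events occurring in the study". The third is a serious protocol violation that makes the drug effect hard to evaluate, with the examples "not taking medicine on time or not participating in the follow-up on time". Unwillingness to continue and loss to follow-up complete the list. No item says whether the granule stops, follow-up stops, or both.

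The Primary outcome section has two endpoints. One is treatment failure over the 4-week treatment period. It covers lack of improvement and worsening, with intubation and ventilator support as examples, and it extends to further events: "or the occurrence of new significant symptoms and signs, or new infection, or death". The other is all-cause mortality at 16 weeks.

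The Participants section says of missing data: "If the data is missing due to dropouts, we will deal with it through statistical methods, such as the intention-to-treat (ITT) analysis". It also promises attempts to trace those lost to follow-up. The Statistical analysis section uses a full analysis set based on the ITT population and compares both primary outcomes by χ² or Fisher's exact test.

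**The concern.** The events that may take a participant out of the trial are largely the events the trial counts, or their precursors. The abstract describes the patients as those "who are incredibly prone to respiratory failure and have a high mortality rate", and the Background cites in-hospital mortality of 55–80%, so these triggers will be common. If a site reads the list as ending follow-up, the participants whose vital status becomes unknown are those most likely to die. That missingness is informative.

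The stated remedy does not help. ITT settles who is analysed and in which arm. It does not supply a week-16 status for someone nobody contacted, and a χ² test of deaths needs a status for every participant.

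At stake are the 16-week mortality comparison and the event rates, which the Sample size section says will feed the sample-size calculation of a further study.

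**Working it through.** **1. Sections side by side.**

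| Ground for withdrawal, dropout or discontinuation | Relation to the primary outcomes |
|---|---|
| Deterioration, e.g. acute respiratory failure | Worsening within 4 weeks is treatment failure; may precede death by week 16 |
| Serious adverse event | Death is a primary event; many others would fit new significant symptoms and signs, but not all |
| Serious protocol violation | Not an outcome event; a post-randomisation adherence criterion |

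**2. Does the list concern only the granule?** The TCM section gives the granule for 4 weeks, and the Study design section adds 12 weeks of follow-up. The deterioration item applies throughout the study period. In weeks 5–16 there is no granule left to stop, so applying the item then can only mean leaving the study. Unwillingness to continue and loss to follow-up are also study exits. The list therefore cannot be read as granule-stopping rules alone.

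**3. Which endpoint is exposed?** Deterioration in the first 4 weeks itself meets the failure definition and can be scored when it happens. A death at, say, week 10 in someone withdrawn at week 2 is recorded only if contact continues. The exposure is mainly 16-week mortality.

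**4. Size, for illustration.** The article gives no assumed rates, power or dropout, so there is no stated figure to reproduce. Taken from the article: 40 per arm. Assumed: true 16-week mortality p of 60% (control) vs 40% (intervention), and a share w of deaths that follow a withdrawal and are not captured.

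- Counted as alive: recorded rate = p(1 − w).
- Excluded: recorded rate = p(1 − w)/(1 − pw).

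At w = 0.5 there are 24 vs 16 true deaths, of which 12 vs 8 are captured.

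- Counted as alive: 12/40 = 30% vs 8/40 = 20%, a difference of 10 points instead of 20.
- Excluded: 12/28 = 43% vs 8/32 = 25%, a difference of 18 points.

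| w | Counted as alive | Difference | Excluded | Difference |
|---|---|---|---|---|
| 0 | 60% vs 40% | 20 | 60% vs 40% | 20 |
| 0.25 | 45% vs 30% | 15 | 53% vs 33% | 20 |
| 0.50 | 30% vs 20% | 10 | 43% vs 25% | 18 |
| 0.75 | 15% vs 10% | 5 | 27% vs 14% | 13 |

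Two-sided 5% power from the pooled two-proportion formula with 40 per arm is 43% for 60% vs 40% and about 18% for 30% vs 20%.

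**5. Other assumed rates, w = 0.5.** For 55% vs 35%, the 20-point difference becomes 10 (counted as alive) or 17 (excluded). For 80% vs 60%, it becomes 10 or 24. Exclusion can thus move the difference either way.

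**6. Cost of unknown status.** With k unknown per arm, the best-case/worst-case range of the risk difference has width 2k/40: k = 4 gives 0.20 and k = 8 gives 0.40.

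**The case against.** A reader might infer that deaths and failures will go uncounted, or that withdrawn participants leave the analysis. The article does not say so. The list has no instruction attached, and nothing states that outcome collection stops or that data are discarded. Several places point the other way:

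- Table 1 schedules mortality at every visit from day 7 to week 16, and deaths are to be recorded at 16 weeks.
- Intubation is counted throughout the study, which presupposes continued observation of deteriorating patients.
- The Safety assessment section has adverse events tracked until resolved or stable.
- Lost participants are to be traced, and the analysis set is ITT-based.

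This stands, and it limits the point to a risk. It does not remove it: none of these places guarantees vital status after withdrawal, and tracing is promised only for those lost to follow-up.

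A reader might also infer that one late dose or visit excludes a participant. The article requires a serious violation that hampers evaluation of the drug, with lateness as an example, and does not say that such participants leave the analysis. The tension with the ITT-based set is real only if the item is applied that way.

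The figures rest on assumed rates and losses, and the fall in power is measured against no stated target in a trial that calls itself exploratory. That too stands.

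Finally, a condensed article may leave detailed withdrawal and missing-data procedures to the full protocol or analysis plan. That excuses missing detail. It does not excuse naming ITT as a missing-data method, or a list that mixes treatment and study exits and overlaps the endpoints.

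**Conclusion.** The point holds as a risk created by the wording. The withdrawal list overlaps the primary-outcome events, does not separate stopping the granule from leaving follow-up, and is paired with a remedy that cannot supply missing outcomes. The main exposure is death by week 16 after withdrawal; 4-week failure is much less exposed.

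Under the assumed 60% vs 40% mortality with a quarter to three quarters of deaths uncaptured, the recorded difference would be 15 down to 5 points if those participants count as alive, or about 20 down to 13 if excluded. Other assumed rates can widen the difference under exclusion, so the direction of distortion is not fixed. If all randomised participants are followed to week 16, there is no loss. The documents do not support the stronger statement that events are in fact being missed.

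**What to change.** - In the Withdrawal section, separate stopping the granule from withdrawal from follow-up. State that stopping the granule for any listed reason does not end follow-up, and limit withdrawal from follow-up to refusal of further contact.
- Ascertain week-16 vital status for all 80 randomised participants, by telephone if needed, and analyse everyone as randomised.
- Count any event that meets the Primary outcome definition within 4 weeks as treatment failure, whatever the granule status.
- Replace the ITT sentence in the Participants section with a missing-outcome rule suited to the binary χ²/Fisher comparison, with a best-case/worst-case sensitivity analysis for unknown 4-week status and unknown vital status. Reserve censoring for a time-to-event analysis of overall survival: it has no place in the binary test, and censoring at an outcome-related withdrawal would itself be informative.

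Which events stop the granule is for the investigators. The Participants, Withdrawal, Primary outcome and Statistical analysis sections must be reconciled.

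The cost is protocol wording, a note to sites and some extra telephone contacts; telephone or WeChat reminders are already planned. The small downside is a wider sensitivity range where status stays unknown. The article reports recruitment as still in progress, so the change could serve participants then under follow-up.

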### Randomization and blinding

The multicenter, dynamic, blocked randomization method is adopted. An independent statistician will produce the random allocation sequence via the PLAN sentences of the Strategic Applications Software (SAS®) Version 9.2 (KEY: FQ37-WSB8-7G5C). After signing the informed consent, the eligible participants will be allocated randomly into either the intervention group or control group at a 1:1 ratio using the SAS9.2 software with a block size of 4. The scheme of random allocation will be obtained from a central stochastic distribution system provided by Jiangsu Famous Medical Technology Co., Ltd. in Nanjing, China.

Except for those responsible for blinding, all participants and investigators will be blinded to the group. The odor and color of Kangxianhuanji granule and placebo look the same, and the packaging is the same. The group’s distribution will not be disclosed unless the researchers had to know the details of the medication being taken by a participant. The study blind will be broken after all participants have finished the study. In case of emergency (such as serious adverse events, or suspected unexpected serious adverse reactions), or when the participant needs to be rescued and must know what kind of treatment the patient has received, the study blind will be opened after consultation of the administrator of research organization.

### Intervention

#### Conventional therapy

All enrolled subjects will receive conventional treatment based on the 2019 Chinese expert consensus for the diagnosis and treatment of AE-IPF [20] and 2018. An official ATS/ERS/JRS/ALAT statement [1]. So far, the pathogenesis of AE-IPF is not clearly understood, and it lacks effective treatment. The current clinical treatment measures mainly include (1) corticosteroids, (2) supplemental oxygen and noninvasive mechanical ventilation, and (3) symptomatic treatment.

#### TCM

The intervention group will be treated with Kangxianhuanji granule, and the control group will be given a placebo granule. Kangxianhuanji granule is a compound herbal medicine, and its main herbs are shown in Table 2. The Kangxianhuanji granule and the placebo granule come in bags, 10 g/bag, and were produced by Jiangyin TianJiang Pharmaceutical Co., Ltd. Each type of granule mixed in water for the oral taking, 10 g each time, twice a day for 4 weeks. Any Chinese herbal medicine or Chinese Patent Medicine with efficacy similar to the experimental drugs will be banned or restricted during the study.

**Table 2 Tab2:** The main components of Kangxianhuanji granule

Chinese name	Latin name	English name	Amount (g)
Ren Shen	Ginseng Radix et Rhizoma	Ginseng	6
Huang Qi	Astragali Radix	Milkvetch root	20
Jiao Gu Lan	Herba GynoStemmae Pentaphilli	Fiveleaf gynostemma	15
Wu Wei Zi	Schisandrae Chinensis Fructus	Chinese magnoliavine fruit	9
Yin Yang Huo	Epimedii Folium	Short-horned Epimedium Herb	9

### Outcomes

#### Primary outcome

Treatment failure rate: The treatment failure is defined as the symptoms or signs that have not improved or worsened (intubation, treatment with a ventilator, etc.), or the occurrence of new significant symptoms and signs, or new infection, or death. The number of treatment failures in two groups was recorded during the treatment period (4 weeks).All-cause mortality at 16 weeks (end of the follow-up): The number of deaths will be recorded at 16 weeks.

